### Fidelity and Adherence

We will observe approximately half of the sessions and use the session’s wireframes as a checklist for fidelity, as well as note taking during session observations concerning participation, engagement, and any deviations from the planned format. When possible, observations will done be in person, and we also will join group Zoom-type meetings. We will assess fidelity (the extent to which the intervention is delivered as intended), dose (how much is delivered), and reach (the proportion of intended recipients participating). A simple email check-in will be a final session component, where participants self-report attendance and indicate session duration. In addition, participants’ visits and time on the Headspace app will be tracked with that app’s analytics.

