12	Wrap-up and next steps for next level	Three-minute guided meditation	Daily 5-minute meditation+visit Headspace app

The program does not require a trained instructor. The coworkers, guided by icons on the screen, are responsible for running the sessions. The initial session has videos and voice-over wireframes, and during session 2, the group-managed format is presented. The group is directed to identify 1 member as the designated facilitator, who follows those icons’ directions. However, being the facilitator requires no preparation or special expertise and other group members can easily assume that role if that individual is not present.

We have used similar coworker-led sessions successfully with other occupational groups [10-12]. We particularly wanted to avoid a hierarchical pedagogic structure of “teaching to” corrections professionals. Peer-led programs have documented efficacy and may be as effective as professionally delivered formats [36,37]. Peers also reduce expenses, promote a sense of shared norms, enhance social support, and augment material with credible examples and personal experiences [38].

To provide a longitudinal program component, we partnered with Headspace, an established effective mindfulness app. In a recent review of mindfulness training apps, Headspace received the highest rating [39]. Individuals will have continuous access to the Headspace app beginning at enrollment for a total of 12 months. Transitioning to more Headspace use is incorporated in the latter weekly sessions to maintain mindfulness once completing the weekly sessions tailored to corrections professionals.

The program is accessible from a simple website portal designed specifically for corrections professionals. It functions on all operating systems. While corrections professionals often do not have their smartphones with them on duty, they do have access to the meeting and breakrooms with computers, tablets, and internet access. A mockup of that the website landing page is shown in Figure 5. Menu pages include (1) the sessions, (2) audio files of guided mindfulness meditations for use during their daily practice, (3) resources with PDFs and links to videos of interest and related to session topics, and (4) Headspace information. For each session, there is a link to play the session, along with buttons to review the video used in that session, and a restatement of the take-home practice opportunities for that session.

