## Discussion

Fifty years ago, Kabat-Zinn et al [65] used Mindfulness-based Stress Reduction to lessen stress and distress for those with chronic pain [65]. MBSR takes time and generally includes a day-long retreat, weekly 2.5-hour classes for 2 months, and daily activities including around 40 minutes of meditation. Although its effectiveness is well established [66], its time commitment is a hurdle*.* Work-related stress is estimated to result in losses of up to US $300 billion annually in the United States [67]. Mindfulness training has gained some traction in the worksite setting [68,69] but still has limited use, partially due to the need for a significant time commitment and an experienced trainer. The innovative format described in this protocol overcomes 3 challenges: time, tailoring, and TWH incorporation. It is delivered in a 30-minute once-a-week, self-directed format and designed specifically for corrections professionals. Importantly, it is incorporated in a TWH context. Mindfulness and TWH are rarely combined. A literature search for TWH and mindfulness yielded only a single citation. Some evidence suggest that mindfulness training may be more effective when combined with other components [70].

Our outcome findings will include three main dimensions: (1) implementation acceptability, observations for fidelity, and adherence; (2) pre- to postsurvey measures of targeted behaviors and in particular dimensions of mindfulness along with measures of inflammation and cellular senescence, in addition to human resource data on missed work, injury claims, and incident reports; and (3) postparticipation survey items relating to program acceptability and focus group interviews concerning for a deeper understanding of practical issues, social validity, and suggestion to improve the program and its use.

The 3 listed dimensions reflect 3 components of this protocol. The first dimension relates to whether we crafted a program that was easy to use and engaging enough to sustain participation, especially in the context of the stressful and generally understaffed context of corrections. The second dimension relates to changes in behaviors with an emphasis on instruments used to assess mindfulness following the usual longer form of mindfulness interventions. The focus group aspect of the third dimension will allow a more thorough understanding of the program, as well as provide suggestions for improvement.

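### In the roughly half of sessions without a staff observer, attendance rests on an end-of-session email self-report, so non-report cannot be told from absence or early exit

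*Protocol article*

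**What the plan says.** All of the following is in the protocol article. The section Fidelity and Adherence names three sources of process data.

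- **Observation.** "We will observe approximately half of the sessions and use the session’s wireframes as a checklist for fidelity". Observers also do "note taking during session observations concerning participation, engagement, and any deviations from the planned format". On mode of observation: "When possible, observations will done be in person, and we also will join group Zoom-type meetings".
- **Email check-in.** "A simple email check-in will be a final session component, where participants self-report attendance and indicate session duration".
- **App analytics.** "participants’ visits and time on the Headspace app will be tracked with that app’s analytics".

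The same section says that the team will assess fidelity, "dose (how much is delivered), and reach (the proportion of intended recipients participating"). Textbox 1 lists session observations as the source for fidelity, dose and reach, under the heading Other and not among the primary or secondary outcomes. The Discussion nevertheless gives as the first of three dimensions of findings "implementation acceptability, observations for fidelity, and adherence", and ties it to whether the program holds people's participation in an understaffed workplace.

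On who runs a session, the Intervention section says: "The group is directed to identify 1 member as the designated facilitator". No trained instructor is needed, and another member can take over if the facilitator is away.

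**The concern.** In an unobserved session the email is the only record described of who was there, and it comes at the end. Someone called back to the unit before the end, someone who stays but sends nothing, and someone who never came can all produce the same result. Session duration is then likely to come mainly from those who stayed to the end.

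What is at stake is the acceptability side of a proof-of-concept trial. If attendance looks low, the team needs to know whether people stopped coming, were called away, or came and did not report, since each points to a different change in the program. A later analysis rule can say how to code a missing check-in, but it cannot recover an absence or early exit that nobody recorded.

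**Working it through.** The article states no attendance or adherence figure, so there is none to reproduce. The check sets the three sources against what each can show, then illustrates the size.

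**What each source can show about attendance at a given session**

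- Observation: can show who was present and who left, but only in about half of the sessions. The article says that notes cover participation; it does not say that attendance is logged by name.
- Email: a positive report shows attendance. No report shows nothing definite.
- Headspace analytics: show app use, not session attendance.

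For the unobserved sessions this leaves the email alone.

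**Inputs**

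- Sessions: 12 (Intervention section).
- Unobserved: 6, taking the stated approximate half as exactly half for every group (assumption).
- Email completion among attendees: r = 0.70 to 0.90 (assumption; the documents give no figure).
- Observers record each attendee, missed emails are independent between sessions, and nobody falsely claims attendance (assumptions).

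**A participant who attends all 12 sessions**

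Credited sessions = 6 + 6r.

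- r = 0.70: 6 + 4.2 = 10.2
- r = 0.90: 6 + 5.4 = 11.4

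Probability of at least one false absence = 1 − r^6.

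- r = 0.70: 1 − 0.118 = 0.882
- r = 0.90: 1 − 0.531 = 0.469

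**Group level.** With true attendance A, measured attendance = 0.5A + 0.5Ar, so the shortfall is 0.5A(1 − r).

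- A = 0.80, r = 0.70: 0.5 × 0.80 × 0.30 = 12 points (68% shown)
- A = 0.80, r = 0.90: 0.5 × 0.80 × 0.10 = 4 points (76% shown)
- Over A = 0.60 to 0.90 (also assumed), the smallest shortfall is 0.5 × 0.60 × 0.10 = 3 points and the largest is 0.5 × 0.90 × 0.30 = 13.5 points.

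**What observation buys.** With no observation, a full attender would be credited with 12r = 8.4 to 10.8 sessions. Observing half the sessions halves the mean shortfall, from 3.6 to 1.8 sessions at r = 0.70 and from 1.2 to 0.6 at r = 0.90. It does not halve the share of full attenders with a false absence: 1 − r^12 is 0.986 and 0.718, against 0.882 and 0.469 with half observed.

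**The case against.** The strongest reply is that this is an ordinary limit of a process measure in a small proof-of-concept trial. The article contradicts nothing here, and a journal article may leave check-in forms to the full protocol. It does not say whether each person or each group sends the email, and a group message listing names would lose less. The email completion rate is assumed, so the figures illustrate size and do not estimate it. All of that stands and keeps the point minor. It does not supply an absence record for the unobserved sessions, which the article does not describe.

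Three stronger readings are tempting, and the document does not support them.

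- A reader might infer that email is the only attendance record in the trial. The same section has staff observing about half of the sessions and noting participation, so the range of 8.4 to 10.8 credited sessions, which treats all 12 as unobserved, does not describe this design.
- A reader might infer that a dropout looks the same as a missed email. The Setting and Participants section commits to tracking every enrolled participant under CONSORT, and surveys follow at 3 and 9 months. Dropouts can therefore be identified at study level; what may stay uncertain is the session at which someone stopped.
- A reader might infer that an efficacy outcome, or the whole dose and reach measure, is wrong. Textbox 1 names observations as the source for dose and reach and places them under Other, and the mixed models use time points, not attendance.

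It is also fair to object that a roster placed only on the last screen would repeat the weakness, because a session cut short would lose the whole group's record. The fix below takes that into account.

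**Conclusion.** The point holds as a minor limitation of measurement. In the roughly half of sessions without an observer, non-report cannot be separated from absence or early exit on the records described, so attendance per participant can be understated. Whether it will be depends on how many attendees send the email, which the documents do not give.

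Under the listed assumptions a full attender loses 0.6 to 1.8 of 12 sessions on average, and about half to nearly nine in ten full attenders carry at least one false absence. If observers do not in fact log attendance by name, the understatement would be larger. The efficacy conclusions do not depend on any of this.

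**What to change.** Add a one-screen roster to each session, completed by that session's designated facilitator. Open it at the start-of-session follow-up and close it at wrap-up. It marks each group member as present to the end, left early or absent, with the session's start and end time. In the first session, before a facilitator has been chosen, any member can fill it in.

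- Treat a missing roster as missing data, not as absence.
- Keep the email as a cross-check.
- Have observers log attendance by name, and use the observed sessions to validate both roster and email. This also yields the email completion rate that had to be assumed above.

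The cost is one form screen per session and no added staff. The small downside is that a coworker, not the participant, reports attendance.

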### Qualitative Data Collection

Following the intervention, we will conduct focus groups concerning program use and outcomes. We will offer partaking in a focus group to all participants. When possible, we will have individuals who went through the sessions together also be together in a focus group. These will last 45 to 60 minutes and will use a trained facilitator and interview guide designed to explore the study outcomes and session observations. The focus group roadmap or interview guide is included in Multimedia Appendix 1. A scribe will take notes and track participant comments.

### Data Analysis

Preliminary analyses will include careful examination of descriptive statistics and distributions for variables at each time point. This will include counts and proportions for categorical variables and means, SDs, and range for continuous variables, as well as 95% CIs for all proportions and means.

### Primary Outcomes

Our primary criterion for determining intervention efficacy will be differences in changes in the primary outcomes listed in Textbox 1. Our primary hypothesis is that the intervention will be associated with an improvement in each of those outcomes. Repeated measures linear mixed effects models will be used to determine whether the outcome measures improved from baseline to post intervention. Models will include terms for the time points T_3_ (0 vs 3 months) and T_9_ (0 vs 9 months), and nested random effects for individuals within sites. Primary analyses will test the significance of the terms to determine whether outcome measures change from baseline to post intervention. Models will adjust for age and gender and follow a purposeful selection strategy to determine which other background characteristics to include. Mixed effects models have the advantage that participants do not need complete data for all 3 time points to be included in the analyses. If after data inspection it is decided to dichotomize some measures, logistic mixed effects models will be used instead.

### Secondary Outcomes and Associations

Secondary outcomes will be analyzed similarly using repeated measures mixed effects models with linear or logistic links depending on whether the outcomes are continuous or binary. We will furthermore analyze whether the changes in primary outcomes are associated with changes in other selected measures. In particular, we hypothesize that (1) reduced stress and healthier behaviors (eg, nutrition, physical activity, and sleep) are associated with improvements in vascular reactivity and cellular senescence and (2) reduced stress and improved perceptions of the organization are associated with reduced injuries and incidents.

### Qualitative Outcomes

We are experienced in mixed methods, having used them successfully in understanding program outcomes [48,59,60]. Analyses of the focus groups following the intervention will involve reiterative pattern analysis of comments, which avoids the substantive bias inherent in a priori categorization. Instead, we will adapt the more inductive constant-comparative method typical of grounded theory [61]. This analysis approach increases the transparency and reproducibility of qualitative research. Our aim is to further explore the findings observed in the primary and secondary outcomes, beginning with a roadmap of questions and exploring the responses. Barriers and enhancements to program impact will be sought within the dynamic contexts of actual experience. Construction of themes and interpretations rather than bounding interpretation with a prespecified list of categories for coding avoids the substantive bias inherent in a priori categorization. Instead, we will use an adaption of the more inductive constant-comparative method [62,63]. Following the identification of themes, the data set will be subjected to microreview in a search for both confirming and disconfirming data. Quotations will be selected to exemplify and elaborate themes, support findings, and illuminate contexts, promoting reader understanding and facilitating. We will use applicable items from the COREQ (Consolidated Criteria for Reporting Qualitative Research) checklist to document and communicate our methods [64]. In addition to providing a deeper understanding of outcomes, the qualitative findings should allow the development of case studies that may be useful in sharing findings with the corrections community.

## Results

As of December 2022, this study is enrolling participants and finalizing the web-based curriculum and website. We anticipate beginning the intervention in early 2023, with data collection to be completed by November of 2023.

## Discussion

Fifty years ago, Kabat-Zinn et al [65] used Mindfulness-based Stress Reduction to lessen stress and distress for those with chronic pain [65]. MBSR takes time and generally includes a day-long retreat, weekly 2.5-hour classes for 2 months, and daily activities including around 40 minutes of meditation. Although its effectiveness is well established [66], its time commitment is a hurdle*.* Work-related stress is estimated to result in losses of up to US $300 billion annually in the United States [67]. Mindfulness training has gained some traction in the worksite setting [68,69] but still has limited use, partially due to the need for a significant time commitment and an experienced trainer. The innovative format described in this protocol overcomes 3 challenges: time, tailoring, and TWH incorporation. It is delivered in a 30-minute once-a-week, self-directed format and designed specifically for corrections professionals. Importantly, it is incorporated in a TWH context. Mindfulness and TWH are rarely combined. A literature search for TWH and mindfulness yielded only a single citation. Some evidence suggest that mindfulness training may be more effective when combined with other components [70].

Our outcome findings will include three main dimensions: (1) implementation acceptability, observations for fidelity, and adherence; (2) pre- to postsurvey measures of targeted behaviors and in particular dimensions of mindfulness along with measures of inflammation and cellular senescence, in addition to human resource data on missed work, injury claims, and incident reports; and (3) postparticipation survey items relating to program acceptability and focus group interviews concerning for a deeper understanding of practical issues, social validity, and suggestion to improve the program and its use.

The 3 listed dimensions reflect 3 components of this protocol. The first dimension relates to whether we crafted a program that was easy to use and engaging enough to sustain participation, especially in the context of the stressful and generally understaffed context of corrections. The second dimension relates to changes in behaviors with an emphasis on instruments used to assess mindfulness following the usual longer form of mindfulness interventions. The focus group aspect of the third dimension will allow a more thorough understanding of the program, as well as provide suggestions for improvement.

We recognize that each correctional system has its unique structural, organizational, and personnel factors and that our findings may not generalize to corrections professionals in other settings. In addition, this is the first evaluation of the peer-led, technology-enabled weekly session and self-directed practice format to increase mindfulness, hence the emphasis on observing sessions and formative qualitative feedback in debriefing after the trial. In addition, participants are not a random sample of these workers. However, we have site-wide data from our previous work [16], and we will be able to compare participants with other corrections professionals from these sites. Despite limitations, the innovative aspects of the program will provide outcome numbers that could inform a subsequent larger randomized controlled trial of the program in this and other settings.

## Appendix

Multimedia Appendix 1 Focus group interview guide.

## Abbreviations

CONSORT: Consolidated Standards of Reporting Trials
COREQ: Consolidated Criteria for Reporting Qualitative Research
DOC: Department of Corrections
IRB: institutional review board
PSS-4: Perceived Stress Scale
OHSU: Oregon Health & Science University
REDCap: Research Electronic Data Capture
TWH: Total Worker Health
